### Intervention Development

The iACTwithPain intervention will be developed by the psychologist members of this research team taking into consideration the psychological flexibility model applied to CP (e.g., Vowles et al., 2009; Dahl and Lundgren, 2016), with the addition of compassion-based elements (Gilbert, 2009; Neff and Germer, 2018) specifically adapted to CP. The research team’s experience on CP’s psychosocial impact and related psychological processes (Carvalho et al., 2018a,b, 2019, 2020), and in developing and delivering ACT and compassion-based interventions to chronically ill populations such as CP, cancer (Trindade et al., 2020), inflammatory bowel disease (ClinicalTrial.gov NCT03840707, undergoing), as well as psychiatric populations (Pinto-Gouveia et al., 2017; ClinicalTrial.gov NCT04101032, undergoing) will be integrated to assure the development of an adequate and rigorous intervention.

### The iACTwithPain Intervention

The iACTwithPain intervention (Table 1) will comprise core themes: (a) theme 1: pain acceptance (psychological flexibility in the presence of thoughts, feelings and behaviors associated with pain through mindfulness and acceptance practices); (b) theme 2: values-based action (promotion of behaviors consistent with personal goals, despite pain symptoms); and (c) theme 3: self-compassion (fostering a compassionate stance toward one’s struggles and suffering), which will only be incorporated in the intervention for experimental condition 2. These themes will be delivered through eight sessions that will be available to participants throughout an 8-week period. Each session will be composed of video-animations, real-image videos, complementary texts, and audio files with the experiential exercises/practices targeting the specific topic of the session. An introductory brief session (session 0) will welcome the participant to the intervention and guide him/her through the use of the platform. From session 1, all sessions will begin with a brief soft-landing exercise. Participants will be asked to complete between-session mindfulness and/or compassion-based meditative exercises as often as they can. These between-session assignments will aim to promote skills introduced in the previous session.

**TABLE 1 T1:** Overview of the iACTwithPain intervention.

**Session**	**Topics**	**In-session exercises/metaphors**	**Between-session assignments**
0	Introduction to the intervention and the platform	Contemplative exercise “Exploring my motivations to do this intervention”	–
1	Psycho-education about chronic pain; The problem with our problem-solving minds (controlling is the problem); Promotion of creative hopelessness; Introduction to mindfulness practice	Mindfulness of breathing practice	Mindfulness of breathing practice
2	Mindfulness as a key aspect to manage suffering; Therapists’ personal experience with mindfulness: Tips for maintaining regular practice; The body as an anchor to the present moment	Mindful movement exercise	Mindful movement exercise; Body scan practice
3	Exploration of the costs of trying to avoid/control pain; Promotion of willingness and acceptance	“What have I stopped doing because of pain?”; Passengers on a bus metaphor; Physicalizing exercise; Quicksand metaphor	Inviting a difficulty exercise
4	The power of thoughts; Promotion of cognitive defusion; Identification of the conceptualized self; Development of the observing self	Imagining an apple exercise; Labeling experiences exercise; The observing self exercise	Mindfulness of sounds and thoughts practice
5	Introduction to compassion: What it is and why we need it; Promotion of feelings of compassion for the self and others	Identification of compassionate sentences exercise; Loving Kindness practice	Informal compassion practice; Loving Kindness practice
6	Continuation of the development of self-compassion; Common obstacles to self-compassion	Safe place and compassionate friend exercise	Informal compassion practice; Safe place and compassionate friend exercise
7	Values definition and clarification	80th birthday exercise; Bull’s eye exercise	Open awareness practice
8	Promotion of committed action; Summary of the intervention and maintenance “kit”; Gratitude practice as farewell	Plans of committed action exercise (choosing values, objectives, and actions, and identifying internal experiences that may pose as obstacles to committed action); Bicycle factory metaphor; Gratitude practice	–

### The ACT-Only Intervention

The ACT-only intervention will follow the same structure and contents as iACTwithPain’s, with the exception of sessions 5 and 6, which, instead of presenting compassion elements, will reinforce and further address willingness, acceptance, defusion, and observing self topics, without adding new information or practices. This intervention will be delivered via the same platform as the iACTwithPain intervention.

### Treatment Integrity

Several aspects of treatment integrity guidelines for ACT (Plumb and Vilardaga, 2010) will be followed during the development of the intervention: (a) integrity was thought as a crucial part of the study, in which therapists′ competence was ensured by previous training in ACT and compassion-based approaches as well as supervision throughout the intervention; (b) the intervention was developed having in mind issues of integrity, by including ACT-consistent informative texts, exercises, and therapist lines and tips in videos; and (c) the intervention was developed following clearly operationalized processes of change from the ACT and compassion-based models.

### Platform Development

The platform will aim at offering access to the interventions’ contents via either personal computers or mobile devices. The platform will have an app-like functioning when accessed from a mobile device. It is based on a well-established CMS that will integrate new modules to support the user registration, enquities, and content delivery on pre-established sequence. The platform will include a set of sessions, each one composed of explanations, video animations, experimental exercises, supplementary texts, support material, daily tasks, audio meditation, and other practices.

Upon the agreement of the patients, usage data will be collected that will have two different purposes: (1) identifying usability issues and (2) understand how pain and suffering should be considered in the interaction design processes. With the exception of data that are required for the RCT, such as usage frequency, most of the usage-related data will be anonymized only keeping the relationships strictly necessary to guide the usability studies. The result of this effort will be to try to maximize the adherence and avoid dropouts due to usability issues and therefore contribute to retain participants in the study.

The platform’s interface design will be based on a calmness-related message. Taking into consideration the target users and the fact that possibly they may be experiencing pain during the usage, all the elements will be designed taking that into account. The simple and flat design approach chosen is expected to eliminate or reduce to a minimum the existence of misleading cues that may induce frustration or distraction.

### Implementation of the Interventions

Participants will follow the sessions in a given order (from session 1 to 8, one session per week). All data will be linked to a data hub tracking participants’ interaction with the platform (i.e., number of logins, duration of interaction with platform, number of visualization of videos/audios, and feedback on each session). Each week, participants will receive an email prompting them to login to the platform and complete the week’s session (that becomes available 1 week after the previous session was completed by the participant). Participants will also receive automatically generated reminders via email with supporting messages: (a) if they do not login for more than 3 days and (b) if they practice continuously (contingency management by reinforcing frequent engagement and practice). This will be particularly important to remind participants to practice the between-session assignments. Contact with the research team will be made available to participants during the intervention period through a one-to-one chat incorporated in the platform. As neither intervention will present risks to participants, a data monitoring committee is not expected to be involved. Adverse events are also not expected. Participants who skip more than two sessions will not be considered for the RCT (in the iACTwithPain group participants who do not complete both of the compassion sessions will be additionally excluded).

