### Primary and Secondary Outcomes in the RCT

Before (T0) and after (T1) the interventions, and in the 3-month (T2) and 6-month (T3) follow-ups, participants in the experimental conditions and in the waiting-list control condition will be assessed through several self-report questionnaires. Participants will receive notifications via email to complete the self-report measures. These data will be collected in the iACTwithPain platform using high standard security mechanisms which will ensure confidentiality. Only the research team will have access to the collected data, including the final dataset, which will be managed by the study’s PI (PC) and kept for 5 years after the study ends. Participants will only be identified by a generated code.

Participants will provide sociodemographic and clinical information and complete self-report measures (in their validated Portuguese versions) to assess primary and secondary outcomes see Table 2.

**TABLE 2 T2:** Schedule of enrollment, interventions, and assessments.

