**Assessments**						
*Primary outcome*						
*PIQ*			X	X	X	X
*Secondary outcomes*						
*MPQ*			X	X	X	X
*HADS*			X	X	X	X
*WHOQOL-bref*			X	X	X	X
*RRQ*			X	X	X	X
*FSCRS*			X	X	X	X
*SCS*			X	X	X	X
*SSPS*			X	X	X	X
*CAMS-R*			X	X	X	X
*CFQ-7*			X	X	X	X
*CompACT*			X	X	X	X
*Intervention’s acceptability questions**				X		

**only for the active conditions.*

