##### Psychological Functioning

Anxiety and depression symptoms will be assessed by the Hospital Anxiety and Depression Scales (HADS; Zigmond and Snaith, 1983; Pais-Ribeiro et al., 2007), in which participants rate the 14 items (7 items for each subscale) on a 4-point scale between 0 and 3 (the scale varies). For each subscale, scores between 0 and 7 are considered normal, 8–10 mild, 11–14 moderate, and 15–21 severe.

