### Statistical Analysis

The efficacy of the iACTwithPain will be assessed by comparing pre-intervention, post-intervention, and 3- and 6-month follow-up questionnaires’ scores through MANOVAs, repeated measures, within-between interaction (with Bonferroni correction). Changes in the primary outcome and in the secondary outcomes between pre-intervention, post-intervention, and follow-ups will be compared between the three conditions (iACT, iACTwithPain, and waiting-list). MANOVAs’ assumptions (multivariate normality, linearity, absence of multicollinearity, and equality of covariance matrices) will be analyzed prior to analysis.

Additionally, changes in painkillers dependence and hospital visits (self-disclosed) will also be compared between the three groups. Cohen’s *d* will be calculated to measure the between-group effect size on both primary and secondary outcomes. Changes in psychological processes (e.g., self-compassion, mindfulness, and psychological flexibility) will also be tested as potential mechanisms of change of the iACTwithPain intervention, using mediation modeling procedures. Missing data will be imputed with PASW Missing Value Analysis (SPSS Inc., United States) (Blankers et al., 2010).

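### The protocol states that the interventions carry no risk and plans no systematic adverse-event collection, so event rates cannot be estimated or compared between arms

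*Protocol article*

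**What the plan says.** Under Implementation of the Interventions, the protocol article gives absence of risk as the reason for lighter oversight: "As neither intervention will present risks to participants, a data monitoring committee is not expected to be involved". The next sentence is "Adverse events are also not expected". No definition, elicitation, recording or reporting of adverse events follows there or elsewhere.

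The assessment points are set out under Primary and Secondary Outcomes in the RCT: "Before (T0) and after (T1) the interventions, and in the 3-month (T2) and 6-month (T3) follow-ups". Table 2 lists eleven scales at all four points. Its last row is "Intervention’s acceptability questions", at T1 only and for the active conditions only. It has no row for adverse or unwanted events.

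Some planned data bear on harm. HADS, PIQ-6 and MPQ are collected at T0 to T3 in all three arms. For HADS the article also gives severity bands: "For each subscale, scores between 0 and 7 are considered normal, 8–10 mild, 11–14 moderate, and 15–21 severe". Statistical Analysis adds that "changes in painkillers dependence and hospital visits (self-disclosed) will also be compared between the three groups". Table 2 does not list those two items.

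Implementation of the Interventions describes one contact channel: "Contact with the research team will be made available to participants during the intervention period through a one-to-one chat". It also records participants' feedback on each session. The same section removes from the trial anyone who skips more than two sessions and, in the iACTwithPain arm, anyone who does not complete both compassion sessions.

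**The concern.** Absence of risk is something a trial can examine; here it is fixed in advance, and the data collection is shaped by it. The article's own content makes the question reasonable to ask. Its Background links chronic pain with psychiatric disorders. Severe psychiatric problems are screened out by self-reported questions. Table 1 includes work on creative hopelessness, on what has been given up because of pain, and on deliberately bringing a difficulty to mind, all delivered as self-management. None of this shows that harm will occur.

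At stake is how a report with no recorded adverse events could be read. Because nobody was asked systematically, it could not separate the absence of events from the absence of a question. The scale scores help only in part. The planned summaries are MANOVAs and Cohen's *d*, which describe group means, and a minority who deteriorate can be hidden inside a mean that improves. The session-skipping rule can act only in the two active arms, because the control arm has no sessions to skip. It could therefore remove worsened participants from one side of the comparison.

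**Working it through.** **Step 1: where could an adverse event enter the data?**

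- *Table 2:* no adverse-event row.
- *Acceptability Assessment:* attrition rate and a satisfaction questionnaire, experimental conditions only. Neither asks about harm.
- *Session feedback:* active arms only by its nature, and not described as a way to capture harm.
- *Chat:* described for the intervention period only, so it does not cover the 3- and 6-month follow-ups. Under Randomization of Participants, the control group gets access to the questionnaires only. Reports made this way would be volunteered and not comparable between arms.
- *HADS, PIQ-6, MPQ:* all arms, T0 to T3. They can show worsening on those scales but not events outside them.
- *Painkiller dependence and hospital visits:* self-disclosed and compared between the three groups. They are relevant to harm but cover two specific matters.

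So adverse-event rates have no numerator in any arm, while two specific self-disclosed outcomes and symptom worsening are available.

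**Step 2: denominators.** The article's sample size is 171 analysable. With 30% drop-out, 171 / 0.70 = 244.3, which becomes 246 when rounded up to three equal arms (3 × 82 = 246). The figure reproduces. The two active arms hold 2 × 82 = 164 participants. If 70% respond, 0.70 × 164 = 114.8, about 115.

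**Step 3: what one systematic question could give if no event were reported.** The one-sided upper 95% bound is U = 1 − 0.05^(1/n), approximated by 3/n.

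| Group | n | 3/n | Exact U |
|---|---|---|---|
| Both active arms, all respond | 164 | 1.8% | 1.8% |
| Both active arms, 70% respond | 115 | 2.6% | 2.6% |
| One active arm, all respond | 82 | 3.7% | 3.6% |
| One active arm, 70% respond | 57 | 5.3% | 5.1% |

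Without the question, no such bound can be calculated for adverse events.

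**Step 4: chance of seeing at least one event in one arm,** 1 − (1 − p)^n, for assumed true rates p. The documents give no rate, so these are assumptions.

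| p | n = 82 | n = 57 |
|---|---|---|
| 1% | 56% | 44% |
| 2% | 81% | 68% |
| 5% | 99% | 95% |

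**Step 5: can the HADS bands alone define worsening?** The bands are "scores between 0 and 7 are considered normal, 8–10 mild, 11–14 moderate, and 15–21 severe". A move from 7 to 8 crosses a band on a one-point change; a move from 11 to 14 is three points and crosses none. Any one-point PIQ-6 change would likewise mix ordinary fluctuation in pain with real deterioration. A useful count needs a stated threshold on the score.

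**The case against.** A reader might infer that the trial schedules no harms data and can support no statement on safety. The documents do not bear that out. Statistical Analysis commits to a three-group comparison of painkiller dependence and hospital visits, and HADS, PIQ-6 and MPQ run to six months in every arm with a concurrent control. It would also be wrong to say that unwanted effects could surface only through the chat.

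A second inference, that the trial will go on to recommend the programme as safe, has no support either. The aims contain no safety objective, and the Discussion's look ahead to wider use is conditional on proven effectiveness and says nothing about safety. The problem arises only if a later report makes a safety claim or is read as making one.

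It can also be said that adverse-event procedures are often condensed in an article, and that a table of worsening is analysis-plan detail which can be built later from stored scores. The second part is fair for the table taken alone. The first part carries less weight here. The article calls itself the first version of the trial's protocol, and it does more than stay silent: it asserts absence of risk and relies on it. Events that were never asked about cannot be reliably recovered afterwards.

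Ethics approval, screening for severe psychiatric problems and continued usual care in all arms are real mitigations. They lower the likely risk but do not measure it. Finally, the zero-event bounds are hypothetical. A broad question put to people with chronic pain over several months may well draw some positive answers, in which case the comparison with the control arm is what matters.

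**Conclusion.** The point holds in this form: the protocol states absence of risk as fact and plans no systematic adverse-event collection, so adverse-event rates cannot be estimated or compared between arms. The evidence on harm that remains is group comparisons of HADS, PIQ-6 and MPQ scores and of self-disclosed painkiller dependence and hospital visits. That evidence is weakened by leaving out participants who skip more than two sessions. The documents do not show that such participants worsened, only that the rule could remove them if they did.

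The size cannot be given as an error in a stated figure, because the protocol states none on harm. The bounds of about 1.8% (164 participants) and 2.6% (115 responders) illustrate what one question could yield. They assume zero events, honest reporting and, for the second, 70% response. The point does not bear on the efficacy conclusions, and it does not amount to saying that the trial can report nothing about safety.

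**What to change.** 1. Under Implementation of the Interventions, replace the wording that neither intervention presents risks and that adverse events are not expected with a statement that unwanted events will be recorded in all arms and reported.
2. Add one self-report item on unwanted events to the T1, T2 and T3 questionnaires in all three arms, and a matching row in Table 2. Word it identically in every arm and do not tie it to the programme, so that the control arm is a valid comparison.
3. Under Statistical Analysis, add one descriptive table by arm giving the number with an unwanted event and the number who worsen from T0 on HADS or PIQ-6. Fix the worsening threshold for each scale in advance, on the score rather than the band, and larger than measurement noise. The documents give no measurement-error figure, so the sponsor has to choose and justify it.
4. State that this table covers every randomised participant with data, whatever sessions they completed, and that those who skip sessions are still invited to T1, T2 and T3. Otherwise the table inherits the loss caused by the session-skipping rule.

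The cost is one extra questionnaire item, one descriptive table and a small added burden on participants. The sample size does not change, and no monitoring committee or clinical rule is proposed.

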### Randomization of Participants

Participants will be randomized (computer-generated random allocation) to one of three conditions: experimental condition 1 (ACT-only intervention); experimental condition 2 (iACTwithPain + self-compassion); and control condition (medical TAU). All participants will continue their treatment as usual for CP. Each participant will be randomly assigned with a number between 1 and 246; after number assignment, participants with numbers 1–82 will be allocated to experimental condition 1, 83–164 to experimental condition 2, and 84–246 to the control condition. Only participants from the experimental conditions will be blind to their allocation; we do not expect any need for unblinding participants in these conditions.

Participants in the two experimental conditions will then access to the respective version of the platform, where they will be asked to complete pre-intervention questionnaires (T0). The control group will only be provided access to the questionnaires.

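### Participants in the two active arms are removed after randomisation for skipping sessions; the rule cannot apply to control, so the efficacy comparison with control is no longer randomised

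*Protocol article*

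**What the plan says.** All references are to the protocol article.

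- **Order of events.** Randomization of Participants allocates people to three conditions. After that, "Participants in the two experimental conditions will then access to the respective version of the platform". For the third arm, "The control group will only be provided access to the questionnaires".
- **Exclusion in the active arms.** Implementation of the Interventions says "Participants who skip more than two sessions will not be considered for the RCT (in the iACTwithPain group" a further criterion is added in the same bracket: "participants who do not complete both of the compassion sessions will be additionally excluded".
- **Unlocking.** The same section has participants follow the sessions in order, each with a weekly session "that becomes available 1 week after the previous session was completed by the participant".
- **Sessions 5 and 6.** Table 1 places the compassion content there. The ACT-Only Intervention keeps the same structure "with the exception of sessions 5 and 6, which, instead of presenting compassion elements", and instead reinforces topics already covered. No completion requirement for these two sessions is stated for ACT-only.
- **Analysis.** Statistical Analysis compares change in the primary and secondary outcomes across the three conditions and adds that "Missing data will be imputed with PASW Missing Value Analysis". It names no analysis population.

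**The concern.** Whether a participant skips sessions is known only after allocation and may depend on the arm and on how the participant is doing. Selecting on it in some arms and not in others means the groups compared are no longer those that randomisation made comparable.

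Control is one of the two comparators in the superiority aim, so the effect reaches the main efficacy question. If people who persist with a self-guided programme would have changed differently without it, the active arms differ from control even when the intervention does nothing. Imputation cannot repair this, because those removed are no longer in the dataset to be imputed.

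The additional iACTwithPain criterion raises a second question: whether the contrast meant to isolate the compassion component also compares differently filtered groups.

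**Working it through.** **1. The plan's own figures.** The sample size is not at fault. A repeated-measures MANOVA within-between interaction with f = 0.25, alpha 0.05, three groups and four measurements first reaches power 0.95 at N = 171 (power 0.951), as stated. Allowing for 30% drop-out, 171 / 0.70 = 244.3, so 245, and 246 for three equal arms of 82. Check: 246 × 0.70 = 172.2, which is at least 171.

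**2. Who can be removed, by arm.**

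| Arm | Sessions | Stated ground for removal |
|---|---|---|
| Control | none | none possible |
| ACT-only | 8 | more than two skipped |
| iACTwithPain | 8 | more than two skipped, or the compassion-session criterion not met |

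The asymmetry against control follows from the text alone.

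**3. Does the extra criterion matter between the two ACT arms?** That depends on whether sessions can be skipped.

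- *Free skipping.* The patterns with at most two of eight sessions missed number 1 + 8 + 28 = 37, and all 37 stay in ACT-only. In iACTwithPain, if both sessions 5 and 6 must be completed, the misses must fall among the other six sessions: 1 + 6 + 15 = 22 patterns stay. If exclusion requires that both be missed, 37 − 1 = 36 stay. These are counts of patterns, not of participants.
- *Strict sequence.* Anyone missing at most two has completed at least the first six sessions, hence 5 and 6. The extra criterion removes nobody more, and the ACT arms are filtered alike.

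**4. Illustrative size against control.** The documents give neither the share excluded nor the link between adherence and outcome, so both are assumptions. Take no treatment effect, a normal adherence score, the lowest share p removed, and correlation r between adherence and untreated change in outcome.

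- Mean shift among those retained = r × φ(z_p) / (1 − p).
- For p = 0.30: z_p = −0.524, φ = 0.348, and 0.348 / 0.70 = 0.497.
- Active arm retained: 82 × 0.70 = 57.4.
- SE with all 82 controls observed: √(1/57.4 + 1/82) = 0.172 SD.
- SE if control also loses 30%, unrelated to outcome: √(2/57.4) = 0.187 SD.
- Two-sided rejection = Φ(−1.96 + shift/SE) + Φ(−1.96 − shift/SE).

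| r | Spurious difference (SD) | Type I error, no control loss | Type I error, 30% control loss |
|---|---|---|---|
| 0.1 | 0.05 | 6.0% | 5.8% |
| 0.2 | 0.10 | 8.9% | 8.3% |
| 0.3 | 0.15 | 13.9% | 12.6% |
| 0.4 | 0.20 | 21.1% | 18.6% |

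A simulation with 6,000 replicates at p = 0.30, r = 0.3 and no control loss gave about 13.4%, in line with the 13.9%.

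**5. Illustrative size between the ACT arms, with free skipping only.** Assume 40% excluded in iACTwithPain and 25% in ACT-only. The multipliers are 0.644 and 0.424, a difference of 0.220. For r = 0.2, 0.3 and 0.4 the shift is 0.04, 0.07 and 0.09 SD. With 49.2 and 61.5 retained, SE = 0.191 and type I error is 5.6%, 6.4% and 7.5%. Under strict sequencing the rule itself creates no such shift.

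**The case against.** **A separate analysis plan may define an all-randomised set.** It may. But the article is not silent: it takes these people out of the RCT itself, so such a plan would contradict a published sentence. The Discussion's remark that engagement will be taken into account in the efficacy test does not bring them back.

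**The stricter filter in iACTwithPain.** A reader might infer that the contrast between the two ACT arms is biased in favour of iACTwithPain. The text does not establish this. Under the unlocking the article describes, the extra criterion has no effect, and under free skipping the illustrated bias is small. What stands is that a separate criterion serves no purpose under strict unlocking, so the two statements need reconciling.

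**Conflict with imputation.** A reader might also infer that excluding non-adherers contradicts the plan to impute. It does not. Controls and session completers can still miss T1, T2 or T3, or single items.

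**The numbers model a simpler test.** This is correct. The calculation uses one mean, whereas the plan tests differences in change over four time points. If adherence relates equally to the outcome at every time point, the shift cancels in change from baseline. Bias requires a correlation with untreated change, which is how r is defined above.

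**Direction.** Early improvers may stop as readily as those doing badly, which would reverse the sign. Nothing in the documents settles it.

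**Conclusion.** The concern holds for the active arms against control. The article states a session-based exclusion that acts after randomisation, operates in two arms, cannot operate in the third, and is not overridden anywhere in the text. Analysed as written, the efficacy comparison with control is not a randomised one. That conclusion needs no numerical assumption.

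The size is illustrative: about 0.10 to 0.20 SD and a type I error of about 8% to 21% in place of 5%, if 30% of an active arm is excluded and r is 0.2 to 0.4, depending on control loss. At r = 0.1 the error rate is about 6%. The bias is smaller if adherence relates only to a stable baseline level, and its direction is assumed.

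For iACTwithPain against ACT-only, the finding is limited to wording that must be reconciled. The sample size is unaffected. The rule should be changed before the trial is analysed, because it is the only analysis-set rule the article states and it governs the primary outcome.

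**What to change.** Replace the exclusion sentence with:

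> All randomised participants are analysed in the arm to which they were allocated, whatever number of sessions they complete, and all are asked for T1–T3 questionnaires.

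Three changes go with it:

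- Time T1, T2 and T3 on the calendar. Because progress is self-paced, someone who stops early otherwise has no defined post-intervention visit.
- Use session completion only for a supportive per-protocol analysis, with the same session-count rule in both ACT arms, and label it non-randomised.
- State whether sessions can be skipped or unlock strictly in sequence, and bring the wording on the compassion sessions into line.

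The cost is a short protocol change and follow-up of non-completers through the email notifications already planned. The estimated effect may be somewhat smaller. The target of 246 need not change.
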